## Integrated Care Guideline Trial

### Full title

Effectiveness of an integrated care guideline training programme on the processes and outcomes of non-communicable chronic diseases in primary care in South Africa: a pragmatic cluster randomised controlled trial.

### Purpose of the study

To evaluate the effectiveness of an integrated guideline-based training programme for primary healthcare nurses and doctors on processes and outcomes of non-communicable chronic diseases, compared with current training and support for chronic diseases.

The corresponding hypothesis is that equipping nurse middle managers as outreach trainers to train primary care staff in integrated adult case management based on a simplified short (101 page), syndromic guideline, can simultaneously improve the quality of care for chronic diseases of lifestyle, chronic respiratory disease and mental health, in resource-constrained non-physician led primary care services.

### Background

The intervention being evaluated in this study is based on PALSA PLUS, or the Practical Approach to Lung Health and HIV/AIDS in South Africa. PALSA PLUS uniquely combines educational outreach, or brief onsite interactive education, with symptom-based or syndromic guidelines (English 2008). Evidence of effectiveness for both components exists (O’Brien 2007, Grimshaw 2003, Hayes 1995, Wawer 1999, Armstrong Schellenberg 2004, El Arifeen 2004). Syndromic approaches have been popularised as tools for health workers in LMICs through the WHO’s programmes for STIs (WHO 1991) and childhood illness (Gove 1997), but have been implemented largely using offsite intensive training approaches with minimal follow-up in the field. This model disadvantages programme rollouts in that it is disruptive to clinical services and limits sustainability and coverage.

Originally drawn from the WHO’s Practical Approach to Lung Health (WHO 2005), PALSA PLUS had been expanded over the past 10 years to include treatment of opportunistic infections in HIV, antiretroviral treatment (initially by doctors and later by non-physicians), STIs and antenatal care. By equipping nurse middle managers as outreach trainers, the programme has become embedded in the healthcare system, and has been able to be implemented at scale. Since mid-2006 over 10,000 healthcare workers in more than a thousand facilities across South African provinces have been reached, and implementation has now started in Malawi.

At each stage of its development, the programme has been subject to rigorous evaluation with pragmatic randomised controlled trials (Fairall 2005, Fairall 2008, Zwarenstein 2010, Schull 2009). Pragmatic trials evaluate the effects of health service interventions under the human, financial and logistic constraints of typical, real world situations (Zwarenstein 2008b, Tunis 2004, Schwartz 1967). The current proposal extends the approach and will evaluate whether the intervention, previously shown to be effective for respiratory diseases including tuberculosis and HIV/AIDS (Fairall 2005, Zwarenstein 2010), will remain effective when expanded to include the primary care management of other major categories of chronic diseases. Specifically, we wish to evaluate whether its effectiveness will be diluted by this broader objective. If successful, this project will provide scientific support for the validity of transversal programmes of care for chronic diseases in primary care in resource-limited settings, with a particular focus in its application to cardiovascular and pulmonary diseases, and its ability to strengthen primary care services.

### Study design

The study is a pragmatic cluster randomised controlled trial with clinics randomised to two parallel arms, and outcomes assessed on individual patients. Clinics will be randomised within health sub-district strata. Stratification is necessary to control for differences in the ratio of infectious to chronic diseases within communities within the Western Cape. Randomisation will be carried out by the trial statistician before the intervention is implemented or patients recruited.

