### Patient recruitment and data collection

This is shared with the validation project and economic evaluation and described in detail under: Recruitment and enrolment (page 25), Research Procedures and Data Collection (Page 26). Patients will be enrolled just before training is due to start in intervention clinics in a sub-district. Patients will be re-interviewed once, 12-15 months after training started in intervention facilities in a sub-district. This is necessary to allow adequate opportunity for health workers to intervene in their care, given that chronic disease patients undergo clinical review 3-6 monthly.

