**Control**

•

Usual care

19

clinics

2299

patients

(121

per clinic)

Follow

-

up:

Clinics

Patients

Follow

-

up:

Clinics

Patients

38 Eden and Overberg clinics

*(stratified by*

*health sub*

*-*

*district)*

INTERVENTION

*Training starts*

PATIENT

INTERVIEWS

Baseline (pre

-

intervention)

Follow

-

up

12

-

16

months post recruitment

Initial:

8

-

12 sessions

over 4 months

Maintenance:

Quarterly

Ongoing

###

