Trained fieldworkers will be responsible for recruitment, enrolment and data collection procedures, under the supervision of the trial co-ordinator, a nursing sister with 20 years’ fieldwork experience in community and clinic-based surveys. In each clinic waiting room patients 18 years or older attending ambulatory services will be invited to be considered for participation in the study, and if willing, will be asked to meet a fieldworker after their consultation with the nurse or doctor and collection of medication from the dispensary. Trained fieldworkers will screen these patients using a structured questionnaire, and eligible patients will be invited to participate further and informed consent will be obtained. Screening and enrolment procedures are summarised in Figure 4.

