The trial co-ordinator will recruit fieldworkers from local community networks, and preference will be given to those with experience in community based surveys. Excellent knowledge of the community will be a pre-requisite to help find participants who do not return to the clinic for follow-up interviews. Fieldworkers will undergo a three to five day training covering: enrolment procedures and consent, measurement of blood pressure and other parameters, use of the handheld computer and general clinic staff liaison and interviewing skills.

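### Clinics are allocated before patients are recruited, and nothing withholds the allocation until enrolment closes, which leaves a route to differential recruitment unprotected

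*Combined protocol and SAP*

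**What the plan says.** The trial is a cluster design with "clinics randomised to two parallel arms, and outcomes assessed on individual patients" (Study design). Figure 3 shows "38 Eden and Overberg clinics" split 19 and 19, with 121 patients per clinic, and the strata are health sub-districts.

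The order of events is explicit. Allocation comes first: "Randomisation will be carried out by the trial statistician before the intervention is implemented or patients recruited". Enrolment follows: "Patients will be enrolled just before training is due to start in intervention clinics in a sub-district" (Patient recruitment and data collection). Research procedures and data collection places recruitment in the month before outreach begins, lasting up to two weeks per clinic and staggered across clinics.

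On who recruits, Recruitment and enrollment states: "Trained fieldworkers will be responsible for recruitment, enrolment and data collection procedures". Adults in the waiting room are invited, then screened after their consultation with a structured questionnaire. No rule fixes which attenders are approached or in what order. Eligibility for the hypertension, diabetes and diagnosed respiratory disease cohorts is by self-report. Symptoms or a CES-D 10 score also admit patients.

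The primary analysis is a GEE logistic model with intervention and stratification factor (trial Data analysis). A secondary analysis restricts the primary outcome to patients poorly controlled at baseline. No section says when the allocation becomes known to fieldworkers, the co-ordinator, trainers or clinic staff.

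**The concern.** Randomising clinics balances clinics. It does not balance the patients who are enrolled after the allocation exists. If anyone involved in enrolment knows the arm, the choice of whom to approach, the effort put into persuasion, or a borderline eligibility judgement can differ between arms. The result is a case-mix difference that randomisation does not protect against.

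This matters here because the primary outcome for three of the four cohorts is treatment intensification, which plausibly depends on how well the patient is controlled at entry. More poorly controlled patients in one arm would shift the crude rate in that arm with no effect of training. The primary model carries no patient-level baseline covariate that would absorb the shift.

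The plan guards against comparable biases elsewhere. Informed consent explains that routine blood results are withheld so that they do not prompt treatment changes, and the Data safety and monitoring plan requires uniform safety handling in both arms. Recruitment has no equivalent protection.

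**Working it through.** **1. The plan's own sample size.** Inputs from Table 1 for diabetes and hypertension: 0.25 v 0.36, ICC 0.04, cluster size 60. There are 19 clinics per arm, power is 85%, and 20% loss is allowed. Alpha is not stated for the sample size; two-sided 0.05 is assumed.

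- Individually randomised n per arm (pooled, no continuity correction) = 314.
- Clinic size m solves 19m / (1 + (m − 1) × 0.04) = 314, so m = 314 × 0.96 / (19 − 314 × 0.04) = 46.8.
- Allowing for loss, 46.8 / 0.8 = 58.5, against the stated 60. The plan's figure is reproduced to rounding.
- With 60 × 0.8 = 48 followed per clinic, the design effect is 1 + 47 × 0.04 = 2.88. Effective n is 19 × 48 / 2.88 = 316.7 per arm, and power is 85.4%.

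The design is sized as claimed. The issue is bias, not power.

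**2. Room for selection.** Characteristics of the study population gives about 10 000 or more attendances a year per clinic. Two weeks is 10 000 × 2/52 ≈ 385 attendances, and 121 / 385 ≈ 31%, or less in busier clinics. This counts attendances, not eligible adults, so the share of eligible patients enrolled could be considerably higher. It shows only that enrolment need not take in every attender.

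**3. Size of a spurious difference under no true effect.** Let q be the share poorly controlled in the control arm, r the ratio of intensification rates (poorly controlled to controlled), and Δ the excess share of poorly controlled patients in intervention clinics. Holding the control rate at 0.25:

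- rate if controlled: c = 0.25 / (q·r + 1 − q); rate if poorly controlled: u = r·c
- spurious difference: d = Δ(u − c); intervention rate: p = 0.25 + d
- SE = √[(0.25 × 0.75 + p(1 − p)) / 316.7]
- rejection probability = 1 − Φ(1.96 − d/SE) + Φ(−1.96 − d/SE)

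Only the upper value of q has a source: the Background reports 33% of hypertensive patients controlled, hence 67% not. The value 50% and all values of r and Δ are assumptions.

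Worked case (q = 0.67, r = 2, Δ = 0.10): c = 0.25 / 1.67 = 0.150; u = 0.299; d = 0.10 × 0.150 = 0.015; p = 0.265; SE = √[(0.1875 + 0.1948) / 316.7] = 0.035; d/SE = 0.43; rejection 7.2%.

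| q | r | Δ (points) | d (points) | OR | Rejection |
|---|---|---|---|---|---|
| 0.67 | 1.5 | 5 | 0.5 | 1.03 | 5.2% |
| 0.67 | 1.5 | 10 | 0.9 | 1.05 | 5.8% |
| 0.67 | 2 | 10 | 1.5 | 1.08 | 7.2% |
| 0.67 | 3 | 10 | 2.1 | 1.12 | 9.4% |
| 0.50 | 3 | 10 | 2.5 | 1.14 | 11.0% |
| 0.67 | 3 | 20 | 4.3 | 1.24 | 22.8% |
| 0.50 | 3 | 20 | 5.0 | 1.29 | 29.2% |

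The planned effect is 11 points, OR (0.36/0.64) / (0.25/0.75) = 1.69. The spurious difference stays below half of it throughout (5.0 / 11 = 45%).

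**The case against.** The strongest reply is that recruiters cannot readily select on control. Fieldworkers invite and screen without measuring it: blood pressure is taken only from eligible, consenting patients, and HbA1C comes later from an outside laboratory. Eligibility for hypertension and diabetes is treated disease, not control, and clinic staff have no stated part in choosing patients. Enrolment also precedes training, so the training itself cannot change who attends. This stands, and it makes large imbalances in control less likely. It does not close the route, because nothing fixes who is approached and nothing hides the arm.

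A second reply is the planned secondary analysis in poorly controlled patients. In the calculation above, those patients have the same rate in both arms, so that analysis would show no spurious effect and would help reveal the artefact. It remains secondary, however. For diabetes it needs baseline HbA1C, and the HbA1C outcome is sized on 20 of the 38 clinics.

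Third, the gradient is uncertain. Adding aspirin or a statin counts as intensification in hypertension and is not tied to blood pressure, and depression case detection has no such control gradient. This is why a range is given, and why it is not carried over to all four cohorts.

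A reader might also infer that fieldworkers will know the arm, since "The trial co-ordinator will recruit fieldworkers from local community networks" and their training covers liaison with clinic staff. The documents do not say so. The statistician allocates, and nurse managers, who are a separate group, deliver the training. The requirement that fieldworkers know the community is there for tracing patients who miss follow-up, and says nothing about allocation.

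**Conclusion.** The concern holds as a gap in protection. Allocation precedes recruitment, recruiters have discretion over whom they approach, no step withholds the allocation until enrolment closes, and the primary model would not remove a case-mix difference. That much rests on the text.

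The stronger reading, that recruitment bias is expected or would be large, is not supported. Neither the size nor the direction can be derived from the documents. Within the assumed ranges the spurious difference is about 0.5 to 5 points against the planned 11, and rejection under no effect is about 5% to 29%. A middle case gives 1.5 points and about 7%. The upper figures need a 20-point imbalance averaged over 19 clinics. The rejection probabilities use a normal approximation with the planned ICC of 0.04 and 48 patients followed per clinic.

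The change is worth making because differential selection cannot be undone once enrolment is complete, and prevention is cheap.

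**What to change.** Keep central randomisation stratified by sub-district. Have the statistician hold each sub-district's allocation and release it to clinics, trainers and the field team only after the last baseline interview in that sub-district. Alternatively, randomise the sub-district at that point. Say so in Study design and in Patient recruitment and data collection. Recruitment is already staggered and timed by sub-district, so this fits the existing schedule.

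The numbers do not change: 38 clinics × 121 = 4598 patients, with power as stated. The cost is protocol wording and scheduling. Trainers and clinics learn their allocation a few weeks later, which shortens preparation for a new trainer group that also takes over PALSA PLUS maintenance at intervention facilities. The plan should confirm that the month between recruitment and outreach can absorb this.

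Keeping follow-up interviewers unaware of the arm and deriving outcomes by program from the recorded medications are separate, optional points. Neither addresses who is enrolled.

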### Characteristics of the study population

Clinics

Public-sector primary care clinics in the Eden and Overberg districts of the Western Cape province which provide care to underserved communities are characterised by high burdens of both infectious and chronic diseases. The 38 largest fixed facilities will be included in the trial (Appendix 1). These clinics service around or more than 10 000 attendances per year, and are staffed by nurse practitioners, doctors and community health workers, all of whom participate in care delivery for chronic diseases. The Eden and Overberg districts have been selected ahead of others, because doctors are in short supply, and services are provided mainly by nurses. This will allow the trial’s results to be generalisable to similar LMIC settings where non-physicians provide care.

Patients

Inclusion criteria:

- Age ≥ 18 years; and
- Planning to reside in the area for the next year; and
- Written consent to participate in the study

Four cohorts are defined. Patients may fulfil inclusion criteria for more than one cohort. Inclusion criteria based on target chronic disease:

| **Target condition** | **Inclusion criteria** |
| --- | --- |
| Hypertension | Self-reported hypertension requiring medication |
| Diabetes | Self-reported diabetes requiring medication |
| Chronic respiratory disease | Self-reported asthma/ chronic bronchitis/ emphysema requiring medication OR  Cough and/or difficult breathing >2 weeks (and not on treatment for tuberculosis in the past 3 months) |
| Depression | The Center for Epidemiologic Studies Depression Scale (CES-D 10 Scale) score of 10 or more (Andresen 1994) |

Exclusion criteria:

- Inability to meet the above criteria
- Acute and/or terminal condition precluding participation such as AIDS or cancer.
- Psychiatric diagnoses precluding participation such as schizophrenia, dementia and other cognitive impairment measured by self report or medical history.
- For chronic respiratory disease: patients who have received tuberculosis treatment in the preceding 3 months will be excluded.

### Endpoints and sample size calculations

The primary endpoint selected for diabetes, hypertension and chronic respiratory disease is ***treatment intensification***, based on research that identifies clinician inertia as a key reason for failure to control these non-communicable chronic diseases (Van Bruggen 2009, Ho 2008, Rodondi 2006, Turchin 2008, Wang 2007). Definition of treatment intensification is dependent on the target condition (Table 1). For depression, ***case detection*** was selected as the primary outcome because the condition is grossly under diagnosed in primary care – as many as 1 in 5 people attending primary care services are suffering from a mental health condition, mostly depression, yet only 5% of those with the condition have been diagnosed.

Background rates and expected effect sizes for diabetes and hypertension were obtained from prior local and international research studies (Charlton 2008, Nau 2004, Grant 2007). Intracluster correlation co-efficients were drawn from published estimates from a number of cluster randomised controlled trials in each disease area (O’Connor, Fairall 2005, Morrell 2009, Rahman 2008). All sample size calculations are for two-sided tests and are powered at 85%. The sample sizes have been inflated by 20% to allow for losses to follow-up at the follow-up interview planned for 12-15 months after recruitment.

We anticipate substantial co-morbidity. Patients with more than one target condition will be eligible for more than one cohort. Based on reported levels on co-morbidity, we estimate that we will need to recruit 121 patients per clinic to realise the sample size for all cohorts (4598 patients in total).

Planned secondary endpoints include disaggregation of primary endpoints, measurement of other processes of care including screening for complications (e.g. dilated eye exams), monitoring control (e.g. annual HbA1C), symptoms (St Georges Respiratory Questionnaire), changes in risk factors for chronic diseases (e.g. systolic blood pressure, waist circumference), productivity, healthcare utilisation, cardiovascular events (e.g. stroke), mortality, newly commenced on simvastatin, and new diagnosis of hypertension , diabetes, chronic respiratory disease, TB and depression.

Due to the considerable burden imposed by venesection, sample size estimates have also been completed for one of the secondary outcomes, HbA1C in diabetic participants. In order to show a difference of 0.5% (8.8% in the control group vs. 8.3% in the intervention group) we need to complete venesection on 30 diabetic patients in 10 clinics in each group (i.e. 600 diabetics from 20 clinics in total). This contains the logistical burden and cost associated with including HbA1C as a secondary outcome. In these calculations, we assumed a standard deviation in HbA1C of 1.2% from the ACCORD trial (Williamson 2007) and an intracluster correlation co-efficient of 0.05.

**Table 1: Primary outcomes and revised sample sizes**

| **Target condition** | **Primary outcome** | **Control** | **Int** | **ICC^1^** | **Required cluster size** | **Cumulative required per clinic** |
| --- | --- | --- | --- | --- | --- | --- |
| Diabetes | Treatment intensification:  Increase in dose of oral hypoglycaemic/ insulin *or*  Addition of new oral hypoglycaemic / insulin *or*  Addition/ increase in dose of ACE inhibitor *or*  Addition of aspirin *or*  Addition/ increase in dose of statin | 0.25 | 0.36 | 0.04 | 60 | 60 |
| Hypertension | Treatment intensification:  Increase in dose of antihypertensive medication *or*  Addition of new antihypertensive *or*  Addition of aspirin *or*  Addition/ increase in dose of statin | 0.25 | 0.36 | 0.04 | 60 | 90^2^ |
| Chronic respiratory disease | Treatment intensification:  Addition of beta-agonist *or*  Addition of ipratropium bromide *or*  Addition of oral theophylline *or*  Addition/ increase in dose of inhaled corticosteroid | 0.15 | 0.25 | 0.02 | 27 | 90^3^ |
| Depression | Case detection:  Started on antidepressant medication *or*  Referred for counselling *or*  Referred to psychiatric services | 0.04 | 0.10 | 0.04 | 60 | 105^4^ |

^1^ ICC: intracluster correlation coefficient

^2^ Assumes 50% of those with diabetes also have hypertension (Steyn 2008 i)

^3^ Assumes 33% of those with either diabetes or hypertension will have a chronic respiratory disease (Ho 2008)

^4^ Assumes 50% of those with diabetes and/or hypertension and/or chronic respiratory disease will score 10 or more on the CESD-10 (Prince 2007).

### Interventions in intervention and control groups

Usual training and support for chronic diseases will continue in both groups. PALSA PLUS training has been implemented throughout the Eden and Overberg districts with over 70% of staff trained by March 2009. This training focuses on infectious disease priorities, but includes chronic respiratory disease because this is required for the integrated case management of tuberculosis suspects. Maintenance of PALSA PLUS training will continue throughout the trial in the control group. This involves infrequent (2 per year) follow-up visits to clinics already trained, distribution and engagement with an annual update of the guideline, and support for nurse trainers including quarterly meetings and monthly newsletters.

A new group of nurse managers will be equipped as outreach trainers for the trial. These managers will assume responsibility for ongoing PALSA PLUS maintenance at intervention facilities, and for the training of staff in the expanded chronic disease content.

### Patient recruitment and data collection

This is shared with the validation project and economic evaluation and described in detail under: Recruitment and enrolment (page 25), Research Procedures and Data Collection (Page 26). Patients will be enrolled just before training is due to start in intervention clinics in a sub-district. Patients will be re-interviewed once, 12-15 months after training started in intervention facilities in a sub-district. This is necessary to allow adequate opportunity for health workers to intervene in their care, given that chronic disease patients undergo clinical review 3-6 monthly.

